### Reproduction of Research Findings (Data Sharing Plan)

*Note: The requirement for a data-sharing plan applies only to studies that are requesting funding at a level greater than \$500,000 in direct costs in any project year. The data sharing plan must:*

- *State that a complete, cleaned, de-identified copy of the final dataset used in conducting the final analyses will be made available within nine months of the end of the final year of funding.*
- *Propose a method by which investigators will make this dataset available if requested.*
- *Propose a budget that would cover costs of data sharing if requested.*

Although a formal data sharing plan is not required for this study, data sharing is an integral part of the many systematic reviews that support the recommendations of existing practice guidelines. We will therefore plan to create a clean, de-identified copy of our final dataset that will be available to other researchers, upon request, within 9 months of the end of the final year of funding. Prior to data sharing, we will remove or convert all identifying information (date of birth will be converted to age and other identifiers will be removed).

There may remain the possibility of deductive disclosure of subjects with unusual characteristics. Thus, we will make the data and associated documentation available to users under a data-sharing agreement that provides for: (1) a commitment to using the data only for research purposes and not to identify any individual participant; (2) a commitment to securing the data using appropriate computer technology; and (3) a commitment to destroying or returning the data after analyses are completed. Data will be saved as SAS or SPSS files, saved to disk, encrypted, and mailed to users. A copy of our analytic code used to generate our primary outcomes paper(s) will also be available on request. Given that this study does not meet the threshold for data sharing requirements, the costs of data preparation and shipping will be borne by the requestor, but since the data files will already be constructed, these costs will be nominal.

## PROTECTION OF HUMAN SUBJECTS

### Risks to the Subjects

#### *Human Subjects Involvement and Characteristics*

The primary research interest of this study is to compare the effectiveness of a standard smoking cessation program versus long-term guided maintenance therapy with nicotine replacement that would support reduction in the amount smoked and set the stage for later quitting. Patients will be eligible for enrollment in this study if they are 18 years of age or older (although smokers younger than 40 are unlikely to have COPD), have physician-diagnosed chronic obstructive pulmonary disease (COPD) (asthma and chronic bronchitis will be included), smoke 5 or more cigarettes per day, have smoked 25 of the past 30 days, and speak either English or Spanish. Patients will be eligible regardless of their interest in quitting. Patients will be excluded if they reside in a facility that doesn't allow smoking (e.g. certain nursing homes), lack access to a telephone, are suffering from a terminal illness with a less than 12 month life expectancy or have an unstable cardiac condition. All patients must be willing to take NRT for up to 12 months, be willing to complete 4 follow-up telephone-based counseling sessions, and be willing to complete 3 follow-up visits. Although no formal assessment of psychiatric illness will be performed, subjects demonstrating markedly inappropriate affect or behavior will be excluded from the study. Everyone who attends a baseline session who is not eligible for the study but interested in quitting will be given self-help materials such as *Clearing the Air*, and will be referred to the state tobacco quitline.

The personnel for this application will complete HIPPA and Human Protection Tutorials Certification prior to starting this project. During the recruitment and informed consent phases, participants will learn about the study and will be informed that their participation is voluntary and that they can withdraw from the study at any time without impacting their current or future health care. Upon enrollment, all enrolled participants will have the highest level of protection of confidentiality for their participation in this study. The potential subject will be given ample opportunity to ask questions prior to agreeing to participate. This entire process will be observed by a witness and will be documented in writing. [name] will be available to answer questions and address any concerns throughout the study. He is available by pager or cell phone 24/7; on dates when he may be unavailable, he will arrange for appropriate study coverage. [name] will retain copies of the signed consent forms throughout the course of the study. Standard language in our consent form assures the participant of the confidential nature of our study. These standards are strictly adhered to and monitored by the University of Kansas Human Subjects Committee. Assigning each participant a study number, numerically coding all data, and secure file storage will maintain confidentiality. A key linking ID-codes and participant's names will be kept on a secure, password-protected server. Only summaries of findings will be reported in any publications or presentations, with no identification of individuals.

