### Participants

**Recruitment.** As part of the Frontiers Clinical and Translational Research program at KUMC, we recently established a research registry that now contains 303 smokers with COPD that have already agreed to be contacted for studies such as this one; this registry is increasing in size daily. We will also recruit from the more than 1,500 smokers with COPD seen each year in the KUMC clinics and hospital. Recruitment of these smokers is enhanced by the use of a real-time, required field in the electronic medical record that identifies smokers when they are first seen. An automated referral system sends a daily list of newly identified smokers to our team of tobacco treatment specialists who can then approach patients about participation in this study. We will also recruit from Swope Health Services, Inc., a Federally Qualified Health Center that has helped us recruit more than 1,500 African American smokers to 4 NIH-funded trials. In the unlikely event that we are

unable to recruit sufficient patients quickly enough at KUMC and Swope, we will extend recruitment to the Midwest Cancer Alliance – hospitals affiliated with the KU Cancer Center, that have helped us recruit almost 1,000 smokers for two other NIH-funded smoking cessation studies, other local pulmonary practices or community venues providing services to smokers.

**Eligibility.** Patients will be eligible for enrollment in this study if they are 18 years of age or older, have physician-diagnosed COPD, smoke 5 or more cigarettes per day, have smoked 25 of the past 30 days (not including days spent in the hospital), and speak either English or Spanish. (Table 1) Patients will be eligible

Table 1. Summary of inclusion and exclusion criteria

| Inclusion Criteria                                                                                                                                                                                                                                                                                                                                                        | Exclusion Criteria                                                                                                                                                                                                                                                                                                                               |

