|---------------------------------------------------------------------------------------------------------------------------------------------------------------------------------------------------------------------------------------------------------------------------------------------------------------------------------------------------------------------------|--------------------------------------------------------------------------------------------------------------------------------------------------------------------------------------------------------------------------------------------------------------------------------------------------------------------------------------------------|
| 
 
• Aged 18 years or older
 
• Physician-diagnosed COPD
 
• Smoke <math>\geq 5</math> cigarettes/day
 
• Smoke cigarettes on <math>\geq 25</math> of the last 30 days
 
• Speak either English or Spanish
 
• Willing to take NRT for up to 1 year and participate in study procedures
 
 | 
 
• Reside in a facility that doesn't allow smoking
 
• Don't have an address and telephone
 
• Unstable cardiac condition (e.g. unstable angina or AMI in past 30 days)
 
• Pregnant or breast feeding
 
• Terminal illness with less than 12 month life expectancy
 
 |

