### Randomization

All eligible participants who consent to participate in the study and complete the baseline data collection will be randomized to either SSC or LT-NRT. Randomization will be determined by computer-generated random numbers and a randomization module embedded in the data capture program.

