| Respiratory function                               | Simple spirometry will be performed at baseline and at the final follow-up visit. (baseline, Mo12)                                                                                                                                                                   |
| Respiratory symptoms                               | Respiratory symptoms will be measured using the COPD Assessment Test (baseline, Mo 3, 6 & 12)                                                                                                                                                                        |
| Respiratory-related hospitalizations and ED visits | Intercurrent hospitalizations and emergency department visits will be assessed at each follow-up visit. Patients will be asked to classify the event as related to their heart or breathing. These will be validated by blinded physician review of medical records. |
| Cardiac-related hospitalizations and ED visits     |                                                                                                                                                                                                                                                                      |

\*Primary outcome

self-report of CPD or they looked at nicotine metabolites (i.e. cotinine). Self-report of CPD is highly problematic, because even if smokers really do reduce the number of cigarettes they smoker, they tend to smoke those cigarettes more efficiently, and cotinine measurements are confounded by the use of therapeutic NRT. Our measures of CO and NNAL will allow us to have objective measure of actual smoke exposure. The NNAL is particularly relevant to our patients who would like to reduce exposure to carcinogens. NNAL (4-(methylnitrosamino)-1-(3)pyridyl-1-butanol) is a pulmonary carcinogen and metabolite of 4-(methylnitrosamino)-1-(3)pyridyl-1-butanone (NNK), a tobacco-specific nitrosamine related to the development of lung cancer. NNAL assessed in urine is highly correlated with smoke-related tobacco exposure.

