### Analytical Plan.

**Sample Size and Power Calculations.** Our sample size was based on our primary outcome, point-prevalence abstinence at Month 12, using an intent-to-treat approach. Based on prior studies using precessation NRT, we estimate a 2-fold increase in cessation outcomes in the LT-NRT group compared to the SSC group. Given our recruitment of patients at all levels of readiness to quit, we estimate a 12 month cessation rate of 10%. With 199 participants, in each arm, we will have an 80% power to detect a 2-fold difference or greater with a Type I error rate of 5%. This sample size will provide comparable power for looking at 6 month sustained cessation. For the CO measured longitudinally at four time points, we have 80% power to detect a mean difference of 2.24 ppm. Likewise, for NNAL, we have 80% power to detect a mean difference of 0.41 pmol/mg creatinine or more between the two groups.

**Specific Aim 1: Compare the benefits of traditional smoking cessation (SSC) versus long-term guided maintenance therapy (LT-NRT) with NRT.** The chi-square test will be used to compare the verified 7-day point prevalence abstinence at Month 12 between the two groups. If there is imbalance between treatment groups at baseline, we will switch to logistic regression for our primary analysis. We will use similar methods to test for group differences for dichotomous secondary outcomes including sustained abstinence and proportion with 1 or more ED visits or hospitalizations. To test for differences in change in respiratory symptoms and FEV1 from baseline measured at 3, 6, and 12 months, we will use standard mixed models repeated measures analysis. Likewise, to test for differences in longitudinal exposure to CO and NNAL, we will compare the area under the curve over the entire 12 months of follow-up using repeated measures analysis. If the treatment differences are heterogeneous across any covariate sub-groups, we will quantify and report such interactions

with appropriate contrast statements. We will compare the cumulative number of self-reported quit attempts by means of a Wilcoxon rank-sum test.

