smoker must successfully complete eligibility screening and provide informed consent before being enrolled in the study. This ensures that all participants meet all inclusion/exclusion criteria as stated in the study protocol and in the informed consent provided to the participant.

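### The data-cleaning rule leaves ineligible people out of the analysis without sparing those already randomized, against intent-to-treat; separately, the COPD entry criterion is stated in two ways

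*Protocol*

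**What the plan says.** **Handling of ineligible people.** The second paragraph of the Data Safety and Monitoring Plan (Protocol) lists data entry and cleaning routines. One of them is a built-in check that marks individuals who fail the eligibility criteria and keeps them out of the analysis. No time point is attached to it, and no distinction is made between randomized and non-randomized people.

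**Analysis principle.** The Analytical Plan, under Sample Size and Power Calculations, bases the sample size on "point-prevalence abstinence at Month 12, using an intent-to-treat approach".

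**Order of events.** Under Randomization: "All eligible participants who consent to participate in the study and complete the baseline data collection will be randomized". Under Recruitment and Informed Consent, screening and consent come before enrollment, and the text adds: "This ensures that all participants meet all inclusion/exclusion criteria as stated in the study protocol".

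**Disease criterion.** The Eligibility paragraph under Participants says that patients qualify if they "have physician-diagnosed COPD, smoke 5 or more cigarettes per day", among other conditions. Table 1 lists "Physician-diagnosed COPD" with no qualifier. The section Human Subjects Involvement and Characteristics repeats the list but adds in parentheses after COPD that "asthma and chronic bronchitis will be included". The same sentence remarks, on the age limit, "although smokers younger than 40 are unlikely to have COPD".

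**The concern.** Intent-to-treat means that everyone randomized is analyzed in the arm assigned. A rule that removes people for failing entry criteria, with no cut-off at randomization, permits removals after assignment. In this trial that matters for two reasons.

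- Treatment is visible. The arms differ in counseling schedule and NRT supply, so staff who reconsider a participant's eligibility may know the arm. The rule does not require the decision to be made without that knowledge.
- Contact differs by arm. LT-NRT participants have 7 counseling sessions through Month 9. SSC participants not interested in quitting within 30 days are offered no further counseling after baseline. Ineligibility could therefore come to light more often in one arm.

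The second matter is separate. If the criterion is read differently from one recruiter to the next, the population behind results labelled as applying to smokers with COPD is not defined. That concerns description and generalization, not the validity of the randomized comparison.

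**Working it through.** The point rests on comparing text. One figure can be reproduced first, to show what it does and does not imply.

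**1. The plan's sample size.** Inputs from Sample Size and Power Calculations: 10% against 20% abstinence (a 2-fold difference), 199 per arm, type I error 5%. Sidedness is not stated, so two-sided is assumed. For a chi-square test without continuity correction:

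power = Φ{[0.10·√n − 1.96·√(2·0.15·0.85)] / √(0.09 + 0.16)}

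With n = 199: [1.411 − 0.990] / 0.5 = 0.842, and Φ(0.842) = 0.800. The stated 80% is reproduced, with no allowance for exclusions (n = 198 gives 79.8%). This does not show that power is lost: the Protocol gives no number or share of participants who would be removed, and if everyone randomized is kept, power for the primary outcome does not change.

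**2. The exclusion rule against intent-to-treat.**

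| Case | Under the data-cleaning rule | Under intent-to-treat | Conflict? |
|---|---|---|---|
| Screened, found ineligible, never randomized | Out of the analysis | Not part of the randomized set | No |
| Randomized, later found not to have met a criterion at entry | Out of the analysis | Analyzed in the assigned arm | Yes |

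The rule's wording covers both rows. It is not tied to any one criterion. An error in reported daily smoking, or a recent cardiac event missed at screening, would trigger it just as a disputed diagnosis would.

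**3. The disease criterion in its different places.**

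| Place | Required diagnosis | Asthma mentioned? |
|---|---|---|
| Participants, Eligibility | Physician-diagnosed COPD | No |
| Table 1 | Physician-diagnosed COPD | No |
| Human Subjects Involvement and Characteristics | Physician-diagnosed COPD, with the added parenthesis | Yes, as included |

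The parenthesis has two readings: (a) a COPD patient who also has asthma is not turned away; (b) asthma counts by itself. Under (a) a smoker with asthma alone is ineligible in all three places. Under (b) that smoker qualifies in the third place and fails in the first two.

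No other criterion decides between them. Baseline spirometry is taken ("Simple spirometry will be performed at baseline and at the final follow-up visit"), but as an outcome and covariate, not as an entry test. The statement that screening guarantees the criteria as written does not help where they are written in two ways. The covariate list in Table 5 has no item for the qualifying diagnosis, only a general health history, so the share with asthma alone might not be recoverable later.

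**The case against.** **The exclusion rule may mean screen failures only.** It sits among data-cleaning routines, not in the Analytical Plan. The database may well hold people who attended a baseline session and were found ineligible, since Participants provides for them. Only eligible people are randomized. This reading is reasonable and would remove the conflict. However, the text does not say it, and a data manager following the sentence literally would remove a randomized participant. What stands is that such cases should be uncommon.

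**Analysis sets are commonly left to the SAP.** That is true, and nothing is held against the Protocol for omitting a definition. The point is that it does state a rule, and the rule as worded clashes with its own analysis principle.

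**The parenthesis may only clarify.** All three places require a physician's diagnosis of COPD, Table 1 is a summary, and the remark "although smokers younger than 40 are unlikely to have COPD" suggests that COPD itself is still needed. This favors reading (a) without settling it. A reader might infer that the Protocol plainly admits asthma alone, but the documents do not go that far.

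**The two points need not be linked.** A reader might infer that asthma-only smokers will be enrolled, later judged ineligible and then dropped. That chain is hypothetical: no step in the Protocol re-examines the diagnosis after randomization, and if asthma does qualify, the rule does not apply to these people. The points are therefore kept apart here.

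**COPD-specific outcomes may not be weakened.** A reader might infer that asthma-only participants would dilute the clinical outcomes. The main event outcome in Table 4 is respiratory-related hospitalizations and ED visits, which would capture asthma events too. COPD-related hospitalization is one of several additional decision-tree models. No size for any dilution can be drawn from the documents.

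**Conclusion.** Both points hold in limited form. The exclusion rule, as worded, permits removal of randomized participants and so conflicts with intent-to-treat. The disease criterion is stated in two ways and leaves open whether asthma without a COPD diagnosis qualifies.

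The number affected is unknown. It is probably small, because eligibility is checked before randomization and recruitment starts from a registry and clinics with identified COPD patients. That source is not exclusive: if numbers fall short, recruitment may extend to community venues, for which no COPD list is described. A table of power under assumed removal rates is tempting, but the documents support no particular rate, so no power loss is claimed. If everyone randomized is analyzed, the abstinence comparison remains valid whichever reading of the criterion is used, and only the description of the population is at stake.

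The conclusion assumes that the two sentences would be followed as written. A shown SAP or data-management manual could already limit the exclusion rule.

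**What to change.** 1. In the Data Safety and Monitoring Plan, reword the check so that it blocks ineligible people before randomization only.
2. State that everyone randomized stays in the primary analysis in the assigned arm. Drop participants later found ineligible only in a sensitivity analysis of Month 12 abstinence.
3. Use one identical disease criterion in the Eligibility paragraph, Table 1, and Human Subjects Involvement and Characteristics, saying whether asthma without a COPD diagnosis qualifies. Requiring a COPD diagnosis, with coexisting asthma allowed, fits the stated aims. If the sponsor intends to admit asthma alone, Table 1 should say so and the population should be described accordingly.
4. Record the qualifying diagnosis at screening.

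The cost is a wording amendment, one screening field and one database rule, with no added visits or tests. If asthma alone is ruled out, the eligible pool may be slightly smaller.

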#### *Sources of Materials*

This study involves testing alternative methods for reducing the harms of smoking and supporting smoking cessation among smokers with COPD. We will provide participants with standardized information on smoking cessation and the appropriate use of NRT. We will gather data from all of our study participants at baseline and months 3, 6, and 12. Information gathered will include surveys, medical records information, measures of respiratory function, urinary measures of nicotine and cigarette smoke exposure, and measures of expired carbon monoxide (to measure smoke exposure). The baseline questionnaire will collect information related to demographics, smoking history, and health status questions. At baseline, 3, 6, and 12 months, we will collect urine specimens, exhaled CO and will administer a brief survey assessing their current smoking, respiratory symptoms, and history of COPD-related hospitalizations or emergency room visits. In addition, at baseline and Month 12, we will collect a measure of their breathing (i.e., spirometry).

All questionnaires and informed consent documents will be submitted to the KUMC IRB for approval prior to implementation.

The KUMC Department of Preventive Medicine and Public Health has a well-developed structure for data management. Working data is maintained on a single large file server. Inactive files are moved to archival storage under control of an automated system, itself controlled by a DBMS (Ingres) based request system that ensures that all data movement is appropriately logged and commented. The archival storage is hosted on the institutional mainframe computer, which also supports billing and registration. The use of the mainframe ensures several high level support functions for the archive system (e.g., storage in separate fire zones, regular copying of data to new media, and guaranteed availability).

The data management will be governed by standard procedures for data security and access. All analyses are logged with respect to IRB authorization, accounting information, principal and co-investigators, statistician, and data analyst involved in the analysis. In order to create a unified data management strategy, we will identify all subjects with a study\_id. To ensure subject confidentiality, no names, social security numbers, hospital or clinic numbers will be included in the shared databases. Names, addresses, telephone numbers, and any other information needed for recruitment, study involvement, and tracking will be obtained and maintained locally by the project personnel. All computer files and systems will be password protected and accessible only by authorized personnel.

